### Analytical and statistical approaches

2.11

Analyses will be performed in three steps. *Step 1* consists of exploratory analyses to identify, correct, and confirm values or missing data, and provide descriptive statistics (frequency [proportions], mean [standard deviations]). *Step 2* focuses on bivariate analyses to compare primary and secondary outcomes by treatment group. We will use t-tests, Wilcoxon rank-sum tests, chi-squared tests, and Fisher's exact tests, as appropriate, for pairwise comparisons between the Navigator and Usual care groups. *Step 3* includes multivariable logistic or linear regression models, as appropriate, to account for potential confounders for the primary and secondary outcomes. The co-primary analysis is pre-specified as use of multivariable linear regression models comparing change in anxiety and change in informational support from enrollment to 30 days after hospital discharge in the Navigator group compared with the Usual care group, after adjusting for potential confounders (i.e., adjusted differences). We pre-defined potential confounders as baseline age (>65 years, yes/no), gender (women vs. men), race (non-Hispanic black vs. other), target health condition (pneumonia, heart failure, COPD, myocardial infarction, sickle cell disease), having a primary care provider (yes/no), patient-reported usual source of healthcare (doctor's office, emergency department, community health center, other), patient-reported hospitalization in the 12 months prior to index hospitalization (yes/no), education (high school or less vs. other), and health insurance (yes/no). To minimize the risk of bias in specifying potential confounders, we will examine the baseline characteristics of study participants while being masked to treatment group allocation before finalizing the list of potential confounders for the multivariable analyses.

All analyses will be conducted using a modified intention-to-treat principle, in which we ignored the individual with the missing data for the co-primary outcomes (complete-case analyses). To assess the sensitivity of results to the complete-case analyses, we will conduct multiple imputations under a missing at random (MAR) assumption [34]. We will also conduct multiple imputations under a missing not at random (MNAR) assumption under a joint selection model of outcome and missingness and employ Bayesian analyses for each of the two co-primary outcomes. Our multi-tiered approach to missing data will be used to determine if the Navigator intervention effects are qualitatively maintained across various approaches to handling missing data. We will also conduct per-protocol analyses (PPAs) for the primary outcome. In the PPAs, the Navigator intervention will be considered per-protocol if the participant received both hospital and home-based components of the CHW-led interventions and at least one peer-coaching call. We will employ a 2-sided Bonferroni-corrected alpha of 0.025 (and 97.5% confidence intervals, CIs) for the two co-primary outcomes in the multivariable analyses, and a 2-sided alpha of 0.05 (and 95% CIs) for all other hypothesis tests.

We will also conduct exploratory analyses to assess the potential for heterogeneity of treatment effects for the primary outcome by examining the consistency of the adjusted differences in pre-specified subgroups (across levels of each baseline characteristic) in a series of linear regression models with covariates that included the treatment-group indicator, the treatment-by-subgroup interaction terms, and all other covariates in the multivariable models. We will also collect a limited number of baseline characteristics in keeping with information that is routinely collected on hospitalizations and that have been associated with hospital readmissions at MSIs [35]. The p-values for consistency of adjusted differences in linear or logistic regression models across subgroups will be determined by Wald chi-squared tests. The PArTNER study was not specifically powered to assess heterogeneity of treatment effects, so all such analyses should be considered exploratory. Due to multiple hypothesis tests, we will employ Bonferroni corrections to reduce the risk of a type 1 error.

A limitation of research directed at improving health systems is that there is often inadequate attention devoted to understanding why an intervention was successful or not successful. Health system interventions are often multi-component, and when they successfully improve care or outcomes, it is helpful to know whether all components of the intervention were necessary for success. Also, when care or outcomes are not improved, it is unclear if barriers to implementation (fidelity) or lack of efficacy contributed to a lack of effect. We therefore will implement a mixed-methods approach to: 1) assess completion of each component of the multi-component Navigator intervention (completion of the barrier assessment, discharge visit, home visit, peer coaching calls) and 2) conduct interviews to debrief with study staff and a convenience sample of participants spanning all five enrollment conditions.

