### Randomization

2.3

Following baseline data collection, we will employ block-stratified randomization with permuted blocks to promote balance in the number of participants in each of the two PArTNER study groups (Navigator intervention and Usual care) in three key baseline participant characteristics: 1) enrollment condition (heart failure, pneumonia, COPD, myocardial infarction, or sickle cell disease); 2) baseline anxiety (Patient Reported Outcomes Measurement Information System [PROMIS] emotional distress-anxiety v1.0, SF4a,T-score ≥50, yes/no); and 3) baseline informational support (PROMIS informational support, v2.0, SF4a, T-score ≥50, yes/no) [27]. The random allocation sequence will be generated by a computerized random number generator. Strata will include baseline values of anxiety (PROMIS emotional distress-anxiety) and informational support (PROMIS informational support), since changes from baseline values for emotional distress-anxiety and informational support at 30 days were the co-primary outcomes. Research staff will be masked to treatment allocation sequence prior to informed consent and baseline data collection as our data system required this information to generate a treatment allocation. Research staff collecting post-randomization outcomes will also be masked to treatment allocation as they do not have access to treatment-related information.

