### Power and sample size

2.4

Assuming 20% attrition and a Bonferroni correction for two co-primary outcomes (2-sided alpha 0.025), we estimate that 1,130 participants (565 participants in each treatment group) are needed for 95% or greater power to detect a 2.5 unit difference (25% of a standard deviation, or T-score of 2.5) for each of the co-primary outcomes in the overall population. The minimum detectable difference in T-score of 2.5 falls well within the T-score minimal clinical important difference (MCID) of 2–5. The 95% power for the primary outcomes was selected to allow the calculated sample size to also provide 80% power to detect a 7.5% absolute reduction in 30-day risk of death or re-hospitalization (from 30% to 22.5%) and 90% power to detect a 10% reduction.

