#### Primary outcomes

2.10.1

Patient and caregiver engagement activities indicated the need for two co-primary outcomes for the clinical trial:1.Change in participant anxiety from baseline (enrollment to 30 days post-discharge).2.Change in participant informational support (enrollment to 30 days post-discharge).

Informational support refers to the ability to obtain advice, guidance, suggestions, or useful information.

We will use the National Institutes of Health (NIH) PROMIS measures for our co-primary outcomes, since the development and validation of PROMIS scales have been extensively documented [27]. The PROMIS emotional distress-anxiety short form (version 1.0 SF4a, 4 items) will be used to assess participant anxiety in the previous 7 days. The PROMIS informational support short form (version 2.0 SF4a, 4 items) will be used to assess informational support among study participants in the previous 7 days. For PROMIS measures, raw scores for each measure will be re-scaled into a standardized T-score with a mean of 50 and standard deviation of 10 for the US general population [27,32,33]. Higher PROMIS T-scores indicate more of the concept being measured (e.g., higher anxiety T-scores indicate more anxiety). Studies suggest that a 2- to 5-unit or greater difference in T-scores is likely to be the MCID, though the MCID following hospital discharge in the target population has not been established.

Using PROMIS measures confers several distinct advantages: 1) *Comparability*—measures have been standardized to be patient-centered, rather than disease-specific, permitting comparisons of patient outcomes between the Navigator and Usual care groups despite enrolling patients with multiple conditions; 2) *Reliability* and *Validity*—metrics for each domain have been rigorously reviewed and tested; 3) *Flexibility*—PROMIS measures can be administered in a variety of ways (in person, telephone, or via computer adaptive testing); for PArTNER, the baseline visit occurred while the patient was in the hospital, so administration was in person. Follow-up visits were performed by telephone to minimize participant burden (a key principle in effectiveness trials); and 4) *Inclusiveness*—PROMIS encompasses all people, regardless of literacy, language, physical function, or life course.

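### The pre-defined covariates for the co-primary change-score models leave out the outcome's baseline PROMIS score and the two PROMIS stratification factors, which costs precision and makes the 97.5% intervals conservative

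*Protocol article*

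**What the plan says.** All references are to the protocol article.

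- **Analytical and statistical approaches (2.11), model.** The co-primary analysis is pre-specified as "multivariable linear regression models comparing change in anxiety and change in informational support from enrollment to 30 days after hospital discharge", Navigator against usual care, with covariate adjustment.
- **Same section, covariates.** The list begins "We pre-defined potential confounders as baseline age (>65 years, yes/no), gender (women vs. men), race (non-Hispanic black vs. other), target health condition" and continues with having a primary care provider, usual source of care, hospitalisation in the prior 12 months, education and insurance. That makes nine covariates, none of them a PROMIS score. The list is to be finalised after the investigators examine baseline characteristics while masked to allocation.
- **Randomization (2.3).** Allocation is stratified by enrolment condition (five levels), baseline anxiety T-score ≥50 and baseline informational support T-score ≥50. "Strata will include baseline values of anxiety (PROMIS emotional distress-anxiety) and informational support (PROMIS informational support" scale), and the stated reason is that change in these scores is the co-primary outcome.
- **Error rate (2.11).** "We will employ a 2-sided Bonferroni-corrected alpha of 0.025 (and 97.5% confidence intervals, CIs) for the two co-primary outcomes in the multivariable analyses".
- **Power and sample size (2.4).** With 20% of participants lost and alpha halved for the two outcomes, the article writes "we estimate that 1,130 participants (565 participants in each treatment group) are needed for 95% or greater power". The target is a difference of 2.5 T-score points, which it equates with a quarter of an SD.
- **Primary outcomes (2.10.1).** The PROMIS measures are put on a "standardized T-score with a mean of 50 and standard deviation of 10 for the US general population".

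Of the three stratification factors, only the health condition is on the covariate list. No other section adds a baseline score or a PROMIS stratum to the model.

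**The concern.** The design treats the two baseline scores as important enough to stratify on, but the listed analysis does not use them. Two consequences follow.

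First, the baseline value is usually the best available predictor of change. A change score modelled without it carries the baseline measurement noise and regression to the mean in its residual variance.

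Second, stratified allocation removes some between-stratum variation from the treatment estimate. A model that leaves the strata out still counts that variation in its standard error. The reported standard error is then larger than the true one, the interval covers more than 97.5%, and the test rejects less often than 2.5% under the null.

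At stake are some power and the width of the main reported intervals.

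**Working it through.** **Inputs from the article.** 565 per arm, 20% attrition, difference 2.5, two-sided alpha 0.025 (critical value 2.241). SD 10 is implied by 2.5 being 25% of an SD. Analysed per arm: 565 × 0.8 = 452.

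**Assumptions.** The baseline-to-30-day correlation rho is not given, so it is varied. SD is 10 at both times. The eight other covariates are taken to explain nothing; so far as they predict the baseline score, the gaps below narrow. Block size is not given, and blocks of 4 are assumed.

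**Step 1: the plan's own figure.** SE = 10 × √(2/452) = 0.665. Power = Φ(2.5/0.665 − 2.241) = Φ(1.517) = 93.5%, close to the stated 95%. SD 10 is the general-population SD of the score. It equals the SD of change only when 2(1 − rho) = 1, that is, at rho 0.5.

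**Step 2: residual SD under each model.**
- Change score without baseline: 10 × √(2(1 − rho)).
- With continuous baseline: 10 × √(1 − rho²).
- Variance ratio, with to without: (1 + rho)/2, below 1 for every rho below 1.

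| rho | SD without | SD with | Power without | Power with | 97.5% CI half-width without | with |
|---|---|---|---|---|---|---|
| 0.2 | 12.65 | 9.80 | 76.7% | 94.5% | 1.89 | 1.46 |
| 0.3 | 11.83 | 9.54 | 82.5% | 95.5% | 1.76 | 1.42 |
| 0.4 | 10.95 | 9.17 | 88.3% | 96.9% | 1.63 | 1.37 |
| 0.5 | 10.00 | 8.66 | 93.5% | 98.2% | 1.49 | 1.29 |
| 0.6 | 8.94 | 8.00 | 97.5% | 99.3% | 1.33 | 1.19 |
| 0.7 | 7.75 | 7.14 | 99.5% | 99.9% | 1.15 | 1.06 |

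If SD 10 is instead the SD of change, the planned model has 93.5% power at any rho. Adding the baseline raises it to 99.5% at rho 0.2, 98.2% at 0.5 and 95.7% at 0.8.

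**Step 3: calibration, by hand.** For a normal score cut at its mean, the split explains 2/π = 0.637 of its variance. The between-stratum part of the change-score variance is therefore about (1 − rho)² × 100 × 0.637. Random loss of 20% after allocation keeps about 0.8 of the benefit of balance. The true variance is then about the model variance minus 0.8 times that part:
- rho 0.3: 140 − 0.8 × 31.2 = 115.0. Model to true SE: √(140/115.0) = 1.10.
- rho 0.5: 100 − 0.8 × 15.9 = 87.3. Ratio 1.07.
- rho 0.7: 60 − 0.8 × 5.73 = 55.4. Ratio 1.04.

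Incomplete blocks reduce these ratios slightly.

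**Step 4: calibration, by simulation.** 1,130 randomised, 20 strata (5 × 2 × 2), blocks of 4, 20% random missingness, condition in the model.

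| rho | Mean model SE | True (empirical) SE | Excess | Type I error (nominal 2.5%) |
|---|---|---|---|---|
| 0.3 | 0.788 | 0.719 | about 10% | about 1.0–1.5% |
| 0.5 | 0.666 | 0.626 | about 6% | about 1.5–1.75% |
| 0.7 | 0.515 | 0.501 | about 3% | about 2% |

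Independent repeats agree in direction. The largest difference was at rho 0.5, where one run of 3,000 gave 0.665 against 0.605. In that run the nominal 97.5% interval covered 98.4%, 98.4% and 98.1% at the three values of rho. With the two PROMIS strata added, coverage was 97.6%, 97.9% and 97.3%.

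**Step 5: power in simulation.** The true SE is smaller than the model SE, so the planned model does a little better than Step 2 suggests. Simulated power without and with baseline was 83.9% and 94.6% at rho 0.3, and 95.2% and 98.5% at rho 0.5. The strata alone gave 90.7% and 97.2%.

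**The case against.** **The list is not closed.** It is to be finalised after a masked look at baseline data, and an analysis plan may exist that is not shown. This stands in part: what can be criticised is the pre-defined list, and the omission can still be repaired. But the article calls the analysis pre-specified and itemises its covariates. It describes them as confounders, and nothing signals that baseline PROMIS scores will be added.

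**The harm is limited.** This stands. A reader might infer that leaving out the baseline biases the treatment comparison or raises the false-positive risk. It does neither: randomisation protects the comparison, and the calibration error is conservative. Stratification already balances both scores at the cut of 50, so only residual imbalance within each half can enter the change score.

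**The size rests on an unstated correlation.** This stands. At rho 0.7 or above the gain is small. A reader might also infer that the trial is underpowered. The article does not support that: the shortfall appears only if SD 10 applies to the score at each time and rho is below about 0.5. If SD 10 is the SD of change, the planned model keeps about 93.5%, and baseline adjustment is extra precision.

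**Secondary outcomes.** The inflated-standard-error argument does not carry over directly to instrumental support, emotional support and global health, because allocation is not stratified on their baselines. Only the efficiency argument does.

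**Conclusion.** The point holds as one of efficiency and calibration that should be corrected. The pre-defined list omits the outcome's baseline score and two of the three stratification factors. Precision is lost at every rho below 1: the standard error without the baseline is larger by a factor of √(2/(1 + rho)), which is 24% at rho 0.3, 15% at 0.5 and 8% at 0.7. The loss of power is material at rho of about 0.5 or below and negligible at 0.7 or above. The co-primary intervals are also conservative, through a standard error about 3% to 10% too large over rho 0.7 to 0.3.

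These sizes rest on an assumed rho, equal SDs of 10, random attrition of 20% and blocks of 4. The direction of the precision loss needs only the equal SDs and rho below 1.

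**What to change.** For each co-primary outcome, pre-specify a linear model with these terms:
- treatment;
- the continuous baseline T-score of that outcome;
- the other co-primary's baseline T-score, or its ≥50 stratum;
- enrolment condition;
- the other listed covariates.

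Fix these terms outright, so that they do not depend on the masked review of baseline characteristics. The 30-day score and the change score give the same treatment estimate once the baseline is in the model, so the outcome definition can stay. For the secondary PROMIS change outcomes, add each outcome's own baseline score for efficiency.

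The cost is wording in the analysis section. Baseline data are collected before randomisation, and the two co-primary scores are already needed to allocate a participant. There is no practical downside.

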### Participants

2.2

Patients hospitalized at UI Health (see Study setting, Section B.6), with a physician diagnosis of heart failure, pneumonia, COPD, myocardial infarction, or sickle cell disease are eligible for study enrollment. Trained research coordinators will use IRB-approved recruitment strategies to screen electronic health records Monday through Saturday to identify hospitalized patients with the target diagnoses. Research coordinators will contact the treating physicians to confirm the admission diagnosis documented in the electronic health record and to obtain verbal assent to approach the patient for enrollment into the study. Written informed consent will be obtained from all participants prior to enrollment. To be eligible, patients need to meet all inclusion criteria and none of the exclusion criteria described in Table 1.

**Table 1 tbl1:** PArTNER study inclusion and exclusion criteria.

Inclusion criteria	Exclusion criteria
1. Hospitalized at UI Health	1.Unable to understand and/or speak English
2. Aged 18 years or older	2. Unable/or declined to give informed consent
3. Index admission physician diagnosis of: - Heart failure, - Pneumonia, - Chronic obstructive pulmonary disease, - Myocardial infarction, or - Sickle cell disease	3. Previous participant in the PArTNER study*
	4. Planned transfer to another acute care facility
	5. Planned discharge to facility other than home (e.g., long term care facility)
	6. Receiving hospice care or planned to be discharged to hospice care
	7. Plan to leave against medical advice

Footer: UI Health – University of Illinois Hospital & Health Sciences System; * refers to patients who were re-hospitalized following completion of participation in the PArTNER study.

**Table 2 tbl2:** Community health worker (CHW)-led interventions implemented in the PArTNER study.

Component of CHW-led intervention	Description
A. Complete barrier assessment linked to socioeconomic resources	• Assessment of need for assistance with employment and income, family and social support, transportation to healthcare facilities, housing, utilities (e.g., heat, light), food, and interpersonal violence. • Barriers selected based on the Society of Hospital Medicine's Project BOOST,^16^ and interviews with stakeholders (patients, caregivers, clinicians, administrators at UI Health). • As appropriate, review barriers with the participant's clinician and social worker.

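### Age is coded only as over 65 or not; continuous age would cost almost nothing and mainly help the exploratory age-interaction test

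*Protocol article*

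**What the plan says.** Protocol article, section 2.11, lists the covariates for the pre-specified co-primary linear models: "We pre-defined potential confounders as baseline age (>65 years, yes/no), gender (women vs. men". The same list includes "target health condition (pneumonia, heart failure, COPD, myocardial infarction, sickle cell disease". Age appears once, as a yes/no variable, and the article gives no reason for the cut.

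Table 1 in section 2.2 sets the age criterion as "Aged 18 years or older", so the lower class runs from 18 to 65.

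For heterogeneity of treatment effects, section 2.11 plans interaction models "by examining the consistency of the adjusted differences in pre-specified subgroups (across levels of each baseline characteristic"). It adds that the trial was not powered for this, "so all such analyses should be considered exploratory", and that Bonferroni corrections will be used.

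The covariate list is still open: baseline characteristics will be examined while masked to allocation "before finalizing the list of potential confounders for the multivariable analyses".

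**The concern.** Forming the split requires each participant's age, so the plan holds finer information than it uses. A single cut at 65 gives the age term the same value at 20 and at 65. That range is wide in a trial that enrols sickle cell disease alongside heart failure, COPD and myocardial infarction.

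Two things are at stake. The first is precision in the adjusted co-primary comparison: the part of the outcome related to age that neither the split nor the other covariates pick up stays in the residual. The second is the age-interaction test. Effectiveness in patient subgroups is the second objective in the abstract, and a test that compares two broad classes cannot use a gradient in treatment effect across age.

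**Working it through.** **The plan's own figure.** The article states no figure on age. The nearest one is the co-primary power in section 2.4 ("Assuming 20% attrition and a Bonferroni correction for two co-primary outcomes (2-sided alpha 0.025"), which serves as the baseline here.
- Inputs: 565 per arm, 20% attrition, difference 2.5, SD 10 (section 2.10.1), two-sided alpha 0.025.
- Completers per arm: 565 × 0.8 = 452, or 904 in total.
- Standard error: 10 × √(2/452) = 0.665. Power = Φ(2.5/0.665 − 2.241) = 0.935, close to the stated 95% or greater.
- For exactly 95%: 2 × (2.241 + 1.645)² × 10²/2.5² gives 484 completers per arm, and 2 × 484/0.8 = 1,210 against the stated 1,130. That gap is a separate matter and does not bear on this point.

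**Information kept by the split.** For normally distributed age and a linear relation, a cut with share p above it keeps φ(c)²/(p(1−p)), where c is the normal quantile at 1−p. The share over 65 is not in the article, so p is varied.

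| Share over 65 | Kept | Lost |
|---|---|---|
| 10% | 0.342 | 66% |
| 20% | 0.280²/0.16 = 0.490 | 51% |
| 30% | 0.576 | 42% |
| 40% | 0.622 | 38% |
| 50% | 0.399²/0.25 = 0.637 | 36% |

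If age were uniform, the share kept would be 3p(1−p): 0.48 at 20% and 0.75 at 50%.

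**With condition in the model.** A simulation assumed 10% to 40% sickle cell patients (mean age 34, SD 11) and other patients with mean age 55 to 65 (SD 14), with ages from 18 to 95. The split plus a sickle cell indicator left 21% to 41% of total age variance unrepresented, or 38% to 59% of the age variance within condition. These age mixes are assumptions.

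**Effect on co-primary power.** At 452 per arm the residual SD is 10 × √(1 − R² × kept), where R² is the assumed share of outcome variance explained by age.

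| R² | Continuous age | Split keeping half | Loss |
|---|---|---|---|
| 1% | 0.9377 | 0.9365 | 0.1 points |
| 2% | 0.9400 | 0.9377 | 0.2 points |
| 5% | 0.9468 | 0.9412 | 0.6 points |

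If only 30% of the information were kept, the loss at R² of 5% would be 0.9468 − 0.9389, or 0.8 points.

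**Effect on the age-interaction test.** Take a linear interaction with 80% power on continuous age at two-sided 0.05. With the split, power = Φ(2.80 × √kept − 1.96).
- 20% over 65: Φ(2.80 × 0.700 − 1.96) = 0.50.
- 50% over 65: Φ(2.80 × 0.798 − 1.96) = 0.61.
- 10% over 65: Φ(2.80 × 0.585 − 1.96) = 0.37.

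The 80% is a reference value, not a power that the plan claims.

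**The case against.** The strongest reply is that this is a modelling preference with almost no effect on the trial's conclusion.

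- **Condition is already a covariate and a randomization stratum**, with sickle cell disease as its own level. It absorbs part of the age contrast between sickle cell and other patients. This stands. A reader might infer that every age difference below 65 falls into the residual; that would be true only of a model with age alone.
- **The outcome is change from baseline**, so stable age differences in score level largely cancel and a high R² for age is unlikely. This stands, and it favours the lower end of the power losses.
- **No age distribution is given.** A reader might take the loss to be half as a fact. That holds only if roughly 15% to 30% of participants are over 65; the article supports a range and no single value.
- **The readmission and death outcomes are binary.** A reader might extend the precision loss to those logistic models. A residual-variance argument does not carry over to them, and no calculation here supports the extension.
- **The subgroup tests are exploratory and Bonferroni-corrected**, and the article does not name the age subgroup. This stands. The same split is nevertheless the natural reading of "pre-specified subgroups (across levels of each baseline characteristic"), because it gives the only age levels stated. The 50% to 61% figures are not the plan's power.
- **A binary split is easy to present**, and the covariate list is not final. Both are true. The first is a reason to keep the split for display, and the second makes the change easy to make.

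**Conclusion.** The point holds as a minor improvement. The plan states a coarser age coding than its data allow and gives no reason for it.

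The coding does not bias the randomized co-primary comparison. Its cost there is about 0.1 to 0.6 power points if age explains 1% to 5% of outcome variance and the split keeps about half of the age information. A reader might infer that the primary result is materially weakened; these figures do not support that.

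The cost that counts is in the exploratory age-interaction test. It rests on roughly normal age, a linear interaction, and the reading that the age subgroup is the same split. The condition main effect offers little help in that test, because what is lost is detail in the treatment-by-age term.

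**What to change.** Enter age as a continuous covariate in the Step 3 models, either linear plus quadratic or as a restricted cubic spline with three knots. Test heterogeneity with a treatment-by-linear-age term, and keep over 65 yes/no only as a display split. Record the choice at the masked baseline review that section 2.11 already provides for, before unmasking, so that pre-specification is preserved.

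The cost is one or two degrees of freedom among about 904 completers (two age terms replace one) and a slightly less simple subgroup presentation.
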